**Figure 11 F11:**
[figure not shown]
An example of a subject wearing the virtual reality and biofeedback equipment.

The systematic desensitization intervention will be structured as follows: the patient will learn a body relaxation technique [diaphragmatic breathing (80)]; the psychotherapist will proceed with the exposure of the patient to the trigger environments in the following order: a psychologist's office, a street with no game-related stimuli, a street with trigger stimuli, an empty tobacco shop, a full tobacco shop with sound stimuli, an empty slot room, a slot room with no audio-video stimuli, a slot room with active slot machines (audio-video stimuli), a slot room with active slot machines and alcohol and tobacco cues. During the virtual exposure to the trigger stimuli, when the patient signals that he/she is feeling a greater psychophysiological activation, the relaxation phase will begin, proceeding according to the following procedure: the patient will be teleported by the therapist to the psychologist's office (cue-free environment), where he/she will activate the radio to start the relaxing music and perform diaphragmatic breathing until psychophysical relaxation is achieved. When the patient is ready for the next exposure to the same trigger stimulus, the therapist will teleport him/her into the previous virtual trigger environment. The therapist will proceed in this way until the end of the time available for the virtual exposure. During the virtual exposure therapy, the psychotherapist will ask the patient to focus on bodily sensations and emerging thoughts and emotions related to gambling craving; after the 20 min of virtual exposure, the topics emerged will be the subject of psychotherapeutic work in the second part of the psychological interview. For both groups, the administration of the scales and questionnaires is scheduled for the nineteenth session; the results of which will be returned in the twentieth session. In the twenty-first session, the follow-up measurements will be carried out 1 month after the end of treatment to also verify the presence of any relapses. In detail, all the steps envisaged by *Alter Game* study are reported with the relative timing in the flow chart below (see Table 1); a total duration of about 18 months is expected (see Table 1).

**Table 1 T1:** Flowchart of Alter Game study.

**Alter game steps**	**Timeline**							
	**Week 0**	**Week 1**	**Week 2**	**8 weeks**	**8 weeks**	**Week 19**	**Week 20**	**Week 25**
Design and implementation of virtual environments								
Hardware and software installation and testing								
Training course for Treatment Providers								
First phone contact with patient								
Patient informed consent obtaining								
Data collection about the patient demographic characteristics, medical history and clinical history concerning GD								
Pre-test (MCMI-III, BIS-11, SOGS, GRCS, MGSES)								
Restitution of pre-test results to the patient								
Inclusion/exclusion criteria + randomization into CBT group and CBT + VR group								
First psychotherapy cycle (8 sessions of traditional psychotherapy for both groups)								
Second psychotherapy cycle (8 sessions of traditional psychotherapy for CBT group and 8 sessions of psychotherapy based on virtual reality for CBT + VR group)								
Post-test (MCMI-III, BIS-11, SOGS, GRCS, MGSES)								
Restitution of post-test results to the patient								
1-month follow-up (MCMI-III, BIS-11, SOGS, GRCS, MGSES)								

*GD, gambling disorder; MCMI-III, Millon Clinical Multiaxial Inventory-III; BIS-11, Barratt Impulsiveness Inventory-11; SOGS, South Oaks Gambling Screen; GRCR, Gambling Related Cognitions Scale; MGSES, Multidimensional Gambling Self-Efficacy Scale; CBT, cognitive behavioral therapy; VR, virtual reality*.

#### Safety and Hygiene Measures

To ensure patient safety and hygiene in the virtual setting, the recommendations of the Italian Higher Institute of Health (HIH) and the following procedures will be followed: (a) Hand cleaning: all subjects trained to handle VR devices shall have an alcohol-based hand sanitizer. Before a user turns on a device, he/she shall wash his/her hands for at least 40 s and following a precise sequence as illustrated on the Ministry of Health website; furthermore, he/she shall use a hydroalcoholic gel, rubbing his/her hands for 20 s (as described by HIH). (b) Ensuring that waterproof foam replacements are fitted to the HMD as the foam present by default does not allow for thorough hygiene. (c) Inserting disposable waterproof masks on HMD before using the viewer and replacing them between patients/treatment providers. (d) Disinfecting joysticks and all objects with which the patients and treatment providers may come into contact in between patients/treatment providers. (e) Sanitizing the EvU-TPS (biofeedback) instrumentation after each use. (f) Patients and treatment providers will be required to wear a surgical mask, respecting the indications of the HIH on the matter. (g) Ensuring that the patient has thoroughly cleaned his/her hands, both with soap and with sanitizing gel before entering the outpatient clinic; in fact, it will not be possible to make him/her wear gloves because of the need to measure psychophysiological parameters by photoplethysmography. (h) Repeating all hygiene procedures in between patients/treatment providers and at the end of each daily session so that the equipment remains sanitized at all times. (i) The hygiene of the surgery and the hospital environment will be guaranteed by the company staff dedicated to this purpose. (l) To sterilize the virtual reality devices, the product TRISEPT COMPLEX will be used, which is available at the warehouses of the internal pharmacy of the G.B. Rossi Hospital of Verona, Italy. (m) The use of an ultraviolet (UV) light box that sterilizes all virtual instrumentation without the use of chemicals that could damage the devices will be considered. Indeed, UV light can damage or destroy various types of viruses such as SARS and MERS (81). At the moment, some companies are working on some prototypes.

## Data Analysis

In general, all the patients' demographic and clinical characteristics will be summarized using descriptive statistical methods. In particular, mean, median, and standard deviations will be used for symmetrically distributed continuous variables, median and interquartile distance for asymmetrically distributed continuous variables, and frequency distributions for categorical variables. Multi-method analysis of craving measurement in order to draw up a physiological and psychometric profile of craving (using biofeedback) will be performed. This analysis will be conducted through linear correlation measures. For the analysis of the efficacy of the training course for the treatment providers, Student's *t*-tests for dependent samples or Wilcoxon's non-parametric test for paired samples will be used. Contingency tables and McNemar tests may also be used. For the analysis of the efficacy of the CBT + VR group compared to the CBT group, a mixed ANOVA will be performed for repeated measures with *Time* as within factor (pre-test/post-test/follow-up) and *Group* as between factor (the CBT + VR group/the CBT group).

Moreover, we will pay attention to the issue of an attrition rate. We are expecting to find a retention rate of at least 80% (78, 79) to avoid that participant loss will bias research outcomes. After that, we will check for any significant difference between the two treatment groups (CBT and CBT + VR) to verify if there is a differential attrition rate. In particular, we will compare the average number of meetings attended by the participants between the two treatment groups through *t*-tests, and we will compare the presence of drop-outs across the two groups through Chi-square tests. Moreover, we will determine if there are any significant differences (at the baseline) between participants who will complete the post-test session and those who will not in order to verify if specific subgroups of participants have a higher drop-out risk. This analysis will be conducted separately for each group. If any significant differences between participants of the two treatment groups will be found, we will verify that systematic attrition does not occur and we will conduct the analyses to verify the effects of the two interventions (CBT and CBT + VR) with the participants who completed the baseline and post-test assessments. Those lost to post tests will be excluded. If significant differences between participants of the two treatment groups will be found for the average number of meetings attended and the treatment drop-out, and participants who will complete the post-test session will be significantly different from those who will not, subsequent analyses will be conducted by using the last observation carried forward (LOCF) to assess the effects of attrition. Furthermore, we will examine within-group changes in outcomes as a function of session attendance to assess the effects of intervention non-compliance on outcomes. These subsequent analyses will be conducted, not excluding participants who will be lost to post-test and by imputing values for the follow-up variables for the participants who will not complete the post-test assessment.

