However, studies on the use of VR with gamblers present some limits. Some studies were conducted on small samples that, sometimes, did not include pathological gamblers (10, 31, 34). Other important weaknesses that could be improved are the following: (a) distinguishing the physical activation due to gambling craving from the one due to possible cybersickness, i.e., discomfort, apathy, nausea, drowsiness, disorientation, eyestrain, and fatigue that may be elicited by an experience in immersive VR (40, 41); (b) using virtual gambling stimuli in association with other virtual addiction triggers (such as alcohol), (c) using VR with other psychotherapeutic techniques, like mindfulness (31); (d) exploring the role of sense of presence in virtual experiences. Sense of presence is a mental manifestation (42), a cognitive state which is consistent with a subjective feeling of “being there,” in a given virtual environment, which is different from the physical one and whose fruition is mediated by a device (43).

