**Figure 8 F8:**
[figure not shown]
A red wine bottle, a wineglass and a lit cigarette in the slot room.

Virtual environments have been created in photorealistic quality and in a “cybersickness-free” mode in order to offer the patient a virtual experience that would be as comfortable as possible, without any unpleasant effects. Indeed, cybersickness consists in a feeling of malaise due to headaches, nausea, vomiting, or dizziness, and it is triggered by the incompatibility between the inputs reaching the brain through the visual sensory channel and those responding to one's real movement (54). To achieve this goal, patients will be able to move within the virtual environment through “real” steps whose movement would be faithfully reproduced in the virtual environment. Moreover, gamblers may use teleportation if the position to be reached is distant and beyond the play area. Through the joystick, it is possible to point to the place to reach, and the virtual experience will restart exactly from the selected point. VR environments run on this VR hardware requirement: (a) HTC Vive PRO Full Kit with a wireless adapter (see Figure 9); (b) PC-Gaming Intel Core i7-9700K—GeForce RTX 2070 8GB-−16GB DDR4-−480GB SSD—Windows 10—Wi-Fi; (c) a 49“ or 55” TV monitor.

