#### Efficacy Evaluation of the Integrated Intervention

##### Design

We will conduct a pre-test/post-test experimental design with a 1-month follow-up.

Two independent groups to which patients will be randomly assigned will be considered. One group will undergo a traditional CBT treatment of 16 sessions (the CBT group), while the second group will undergo the integrated treatment, consisting of 8 CBT sessions and 8 sessions of psychotherapy based on VR cue-exposure therapy, each with a different environment (the CBT + VR group). Each session will last 1 h. To better control the effects of the training in VR on pathological gamblers, the psychophysiological parameters of craving will be measured through biofeedback and VAS at each session of the training (multi-method measurement of craving).

To verify the efficacy of the intervention, one measurement session is planned before the beginning of the treatment (pre-test), and one at the end of the treatment (post-test). For the assessment of the maintenance of any changes at post-test, an additional measurement is planned 1 month after the end of the treatment (follow-up). The three measurement sessions are planned for both the CBT group and the CBT + VR group. In each measurement session, perceived self-efficacy in managing gambling behavior, craving, gambling-related cognitive distortions, impulsivity, personality traits, and pathological gambling symptoms will be measured in both groups.

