Patients meeting the inclusion criteria will be randomly assigned to the CBT group or to the CBT + VR group. The CBT group will follow a full cycle of psychotherapy that will consist of 16 weekly sessions, lasting 60 min and will make use of techniques belonging to an evidence-based cognitive-behavioral approach. For the CBT + VR group, there will be a first cycle of traditional psychotherapy that will consist of 8 weekly sessions, each lasting 60 min, which will also make use of evidence-based cognitive-behavioral approach techniques. Following this, psychotherapy based on virtual exposure will be carried out, which will again comprise 8 weekly sessions, marked by: systematic desensitization therapy in virtual reality exposure therapy, cognitive restructuring, and emotional management/literacy. Each virtual session will last 60 min, 20 min of which will be dedicated to virtual exposure. About 20 mins is the recommended limit of the duration of immersions in virtual reality because eyestrain and headache may occur for longer exposures (76, 77). We adopted this safety limit at least until empirical data document the safety of VR immersion with gamblers (10). An extinction process needs more time to originate, but limiting the duration of the immersion is necessary due to ethical considerations (10).

The virtual session will be structured as follows. In the first session, the virtual protocol will be presented to the patient, and virtual training will be carried out to provide the skills related to the use of the instrumentation (Figure 11). Biofeedback parameters will also be measured 5 min before the session. From the second to the eighth sessions, the biofeedback parameters will be measured 5 min before the beginning of the session (in the study, the baseline rate), and the measurements will be resumed during the entire exposure to the virtual environment. The patient will be asked about the intensity of the craving felt during both measurements and at the end of each session *via* VAS. As mentioned above, the technique used in conjunction with virtual cue exposure therapy will be systematic desensitization, which is a psychotherapeutic CBT treatment consisting in alternating phases of exposure to the trigger cues to phases of bodily relaxation, with the aim of reinforcing the relaxation response even in the presence of specific reactive cues (78, 79).

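### The craving profile rests on linear correlation of readings repeated within patients, with the patient not named as the cluster; pooling them would inflate false positives and blur what the correlation means

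*Protocol article*

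**What the plan says.** The Data Analysis section plans a multi-method craving analysis "in order to draw up a physiological and psychometric profile of craving (using biofeedback) will be performed" and continues: "This analysis will be conducted through linear correlation measures". It gives no unit of analysis, no rule for repeated readings, and no hypothesis or significance level for this analysis. The repeated-measures mixed ANOVA later in the section is for the comparison of CBT + VR with CBT only.

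The data are repeated by design. Under Design, "the psychophysiological parameters of craving will be measured through biofeedback and VAS at each session of the training". Under Intervention, the VR phase is one "which will again comprise 8 weekly sessions". From the second session "the biofeedback parameters will be measured 5 min before the beginning of the session (in the study, the baseline rate"), and recording resumes for the whole exposure. On the VAS, "The patient will be asked about the intensity of the craving felt during both measurements and at the end of each session". The section on multidimensional craving measurement lists four physiological measures (heart rate, heart rate variability, skin conductance, skin temperature) and places these measurements in VR therapy, so they come from the CBT + VR arm.

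**The concern.** A standard test of a linear correlation takes every pair as independent. Readings from one patient are not: some people run a high heart rate or report high craving at every session. If all pairs go into one coefficient, the test counts far more information than about 30 people supply.

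The coefficient would also be hard to interpret, even as description. It combines two questions: whether patients with more arousal report more craving, and whether craving rises in a patient when that patient's arousal rises. The Introduction's rationale, that gambling cues may provoke craving and arousal together, concerns the second. The Discussion relies on biofeedback to get past the limits of self-report, and correlation is the only analysis named for it. At stake is whether a reported physiology-craving link can be believed and what it means.

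**Working it through.** **Plan's own figure.** None is given for this analysis. The article's only sample-size figure, n = 58 under Recruitment, belongs to the mixed ANOVA. It reproduces as a between-group effect with f = 0.40, three occasions and an assumed correlation of 0.5 (power 0.956), and has no bearing here.

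**Inputs from the article**
- Patients: about 60 in two randomised groups. The ratio is not stated; 1:1 gives 60 / 2 = 30 in the VR arm, or 0.80 × 30 = 24 at the expected 80% retention.
- Pairs per patient: sessions 2 to 8 with two paired readings each, 7 × 2 = 14. Exposure readings alone give 7. The end-of-session VAS has no matching recording.
- Physiological measures: 4.

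**Assumption.** The share of variance lying between patients (ICC) is not given. A range of 0.1 to 0.7 is shown, equal for both variables.

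**Formula.** With no true association at either level, m pairs per patient inflate the variance of a pooled Pearson r by about D = 1 + (m − 1) × ICC_x × ICC_y. The true rejection rate of a nominal 5% test is then about 2 × [1 − Φ(1.96 / √D)].

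Example, m = 14 and both ICCs 0.5: D = 1 + 13 × 0.25 = 4.25; 1.96 / 2.06 = 0.95; rate = 34%. The 30 × 14 = 420 pairs are worth about 420 / 4.25 = 99.

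**Results for 30 patients** (simulation, 20,000 runs per cell)

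| ICC (both) | D, 14 pairs | Formula | Simulated | D, 7 pairs | Formula | Simulated |
|---|---|---|---|---|---|---|
| 0.1 | 1.13 | 6.5% | 6.5% | 1.06 | 5.7% | 5.4% |
| 0.3 | 2.17 | 18.3% | 17.8% | 1.54 | 11.4% | 11.5% |
| 0.5 | 4.25 | 34.2% | 34.5% | 2.50 | 21.5% | 21.0% |
| 0.7 | 7.37 | 47.0% | 48.3% | 3.94 | 32.3% | 32.6% |

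With 24 patients and 14 pairs the simulated rates are 6.4%, 18.3%, 34.1% and 48.1%, so retention hardly matters.

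**Other ways to handle the repeats** (30 patients, 14 pairs, ICC 0.5)
- One mean per patient: 4.9%. Valid, but it answers only the between-patient question.
- One occasion per patient: 5.0% per test. Doing this for every occasion and measure makes 14 × 4 = 56 tests, with 56 × 0.05 = 2.8 false positives expected.
- Repeated-measures (within-patient) correlation: 5.2%.

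**Why condition is needed as a term.** Suppose exposure raises both variables by 0.5 SD (assumed) with no other link. A repeated-measures correlation without condition then rejects 65% of the time; with condition removed it rejects 4.8%. Without the term, the coefficient may show only that both readings are higher during exposure.

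**The case against.** The strongest reply is that the article does not commit to pooling. Its wording is generic, and repeated-measures correlation is itself a linear correlation measure. No significance test is tied to the profile, the ICCs are outside assumptions, and a condensed article may leave such detail to a fuller document. Much of this stands. A reader might infer that physiology-craving links will look significant far too often. The text does not support that: it states neither pooling nor testing, two of the simple alternatives hold about 5% per test, and at an ICC of 0.1 the inflation is slight. A between-patient correlation is also a legitimate part of a psychometric profile.

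What remains is that a method is named, the data it must handle are clustered, and the plain readings of that method either misstate the evidence or miss the within-patient question.

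A reader might also infer that movement during exposure leaves unaddressed a weakness the Introduction lists. That weakness is "distinguishing the physical activation due to gambling craving from the one due to possible cybersickness", so it concerns cybersickness and not walking. The section on the virtual environments introduces physical steps ("patients will be able to move within the virtual environment through" them) and teleportation precisely to limit cybersickness, and Recruitment withdraws patients who have it in two consecutive virtual sessions. The article gives no figure for the effect of movement on the recordings. This inference should not be drawn.

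**Conclusion.** The concern holds conditionally. If readings are pooled and tested as independent, the false-positive rate is about 18 to 48% with 14 pairs per patient and about 11 to 33% with 7, for ICCs of 0.3 to 0.7; at 0.1 it is about 5 to 7%. These figures assume 1:1 allocation, equal ICCs for both variables, no true association, and constant correlation within a patient with no trend over sessions. The mixing of between- and within-patient association does not depend on any test being done. It affects a secondary, descriptive analysis, so the change is advisable rather than essential.

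**What to change.** In Data Analysis, name the patient as the cluster for the craving profile and replace the general reference to linear correlation with one of:

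- a linear mixed model of VAS on each physiological measure, with a patient random intercept, terms for session and for condition (pre-session or exposure), and the physiological measure split into the patient's own mean (between-patient part) and the deviation from it (within-patient part); or
- repeated-measures correlation, adjusted for session and condition, with the correlation of patient means reported separately.

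Report the pre-session to exposure change in VAS and in each measure alongside, because the condition term takes that shared shift out of the within-patient coefficient. Present the four measures as estimates with confidence intervals. If they are tested, note that four independent tests at 5% already give 1 − 0.95^4 = 18.5% for at least one false positive.

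Any contrast of cue-free with cued versions of a setting should be labelled exploratory. In the fixed exposure order the cue-free version always comes first, often in a different session, so the contrast is confounded with time and habituation.

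The cost is analysis wording only: the readings are already planned. If a fuller analysis plan already specifies this, a cross-reference is enough.
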